## Abstract

**Background::**

Stroke survivors are accompanied by dysfunctions, greatly declining their activities of daily living and bringing burden to families and societies. Although modern rehabilitation therapy has a systematic program in post-stroke motor rehabilitation, numbers of patients still recover slowly. Eye-acupuncture (EA), as an important type of acupuncture, has been widely applied effectively in rehabilitation of stroke for about 50 years. So we combine EA with modern rehabilitation which has achieved successful results. Therefore, we need to adopt an objective and accurate evaluation method to study the effect of this method.

**Methods::**

We aim to design a multi-center, block randomized, parallel control trial to assess the effect of eye-acupuncture combined with rehabilitation training therapy for patients with hemiplegia in the convalescent stage of stroke. 360 patients will be enrolled from 6 centres, with half of them (n = 180) in the control group (routine treatment group) and others (n = 180) in the experimental group (eye-acupuncture combined with routine treatment group). Stratified block randomization will be used in the study and the serial number 001-360 which corresponds to a participant will be assigned to each center randomly. We will use the sequentially sealed envelopes to hide the generating of assignment sequence. The cases of dropouts will be recorded with reasons. And the clinical CRFs will be filled in accurately, completely, and timely for statistical analysis.

**Results::**

To verify the clinical effects, we will measure the change of bellows from visit 1 to visit 4. Primary outcomes: activity of daily living (ADL) scales (modified Barthel index); simple Fugl–Meyer motor function score; functional magnetic resonance imaging (fMRI) of the brain in the resting state. Secondary outcomes: traditional Chinese medicine (TCM) syndrome score scale; western aphasia battery (WAB); water swallow test; Montreal cognitive assessment (MoCA); growth-associated protein-43 (GAP-43); microtubule-associated protein-2 (MAP-2).

**Conclusion::**

The results of this study will provide present evidence on assessing effectiveness of EA combined with rehabilitation training for patients with hemiplegia in the convalescent stage of stroke.

**Trial registration::**

This trial has been registrated in Chinese Clinical Trail Registry with the registration number as ChiCTR1900027835 (http://www.chictr.org.cn/).

## Introduction

1

Stroke is defined as an acute neurologic dysfunction syndrome caused by local blood circulation disorder in the brain, with high levels of morbidity, mortality, recurrence, and disability.^[1,2]^ Nowadays more patients get timely effective treatment and successfully survive after the acute stage. However, most stroke survivors are accompanied by dysfunctions in many aspects, such as dyskinesia, dysphagia, sensory, speech, and cognitive disorder, declining their activities of daily living and bringing burden to families and societies.^[3–5]^ So it is important to take comprehensive and effective rehabilitation treatment as soon as possible. Hemiplegia is one of the major post-stroke dysfunctions and has the greatest impact on activities of daily living.^[6]^ Modern rehabilitation medicine has a systematic program in post-stroke motor rehabilitation. While a large number of patients in the convalescent stage of stroke still encounter bottleneck and recover slowly or stagnantly for a long time.^[7–9]^ So we try to combine traditional Chinese medicine rehabilitation with modern rehabilitation.

Acupuncture is one of the main therapies in traditional Chinese medicine rehabilitation and clinical effectiveness has been confirmed. As a common fine-needle acupuncture therapy, eye-acupuncture is widely applied in rehabilitation of stroke.^[10–14]^ We combine eye-acupuncture (EA) with physical therapy and occupational therapy in modern rehabilitation to achieve better results and put forward an innovative method in the treatment of motor dysfunction after stroke by eye-acupuncture combined with rehabilitation training therapy. The success of rehabilitation requires effective methods and objective evaluation. The scaling method in modern rehabilitation is often applied to evaluate the effect of motor dysfunction after stroke due to its high reliability and validity. However, with the wide application of traditional Chinese medicine rehabilitation, there is still a lack of corresponding therapeutic evaluation methods and objective evaluation indicators about stroke in traditional Chinese medicine (TCM). As a result, we need to adopt an objective and accurate evaluation method to study about the effect of eye-acupuncture with rehabilitation training therapy in motor dysfunction after stroke, which may benefit the further promotion in primary hospitals.

## Methods/design

2

### Study design

2.1

A multi-center, block randomized, parallel control trial has been designed to assess the effect of eye-acupuncture combined with rehabilitation training therapy on limb dysfunction in patients with stroke in the convalescent stage. 360 patients will be enrolled. In order to verify and evaluate the clinical effects, outcomes will be measured by the activity of daily living (ADL) scales (modified Barthel index), modified Rankin scales (MRS), TCM syndrome score, simple Fugl–Meyer motor function score, water swallow test, western aphasia battery (WAB), Montreal cognitive assessment (MoCA) and 2 brain function remodeling indexes, growth-associated protein-43 (GAP-43), and microtubule-associated protein-2 (MAP-2) in the infarction border zone. It is expected to develop the technical standards of eye-acupuncture combined with rehabilitation training therapy, to form the characteristic TCM rehabilitation technology and diagnosis and treatment of stroke in the convalescent stage, to optimize the outcome assessment and to form the characteristic TCM rehabilitation evaluation method and hierarchical medical treatment system.

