### Inclusion criteria

3.3

Age 30 to 75 years;Meet the diagnostic criteria for cerebral infarction and intracerebral hemorrhage;Meet the diagnostic criteria for stroke and staging criterion in traditional Chinese medicine,The onset time of cerebral infarction or intracerebral hemorrhage is within 3 months; the evaluation of modified Barthel index is less than 70 points, and the evaluation of modified Rankin scale is more than 3 points;Modified Barthel index < 70, MRS ≥ 3;Patients and his family members both voluntarily agree to participate in this clinical trial and sign the informed consent.

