### Exclusion criteria

3.4

(1)Lacking definitive imaging examination, such as CT or MRI.(2)Special types of stroke: individuals with progressive stroke or intracerebral hemorrhage after cerebral infarction or with disturbance of consciousness.(3)Individuals with mild syndrome; individuals with slight stroke or slight neurological defect and the evaluation of modified Barthel index is more than 70 points; individuals without disability or with rapid improvement of symptoms, such as individuals with the transient ischemic attack (TIA) and (RIND).(4)Individuals who receive treatment of dredging blocking vessels in the acute stage (such as thrombolysis, arterial thrombectomy, super early thrombus aspiration, and stenting).(5)Individuals with bleeding tendency; individuals with serious bleeding within 3 months.(6)Individuals with severe cardiac insufficiency, atrial fibrillation, heart valve disease, or individuals after heart valve replacement.(7)Individuals with other diseases, which can influence the function of limb movement; individuals with limb motor dysfunction caused by claudication, rheumatoid arthritis, or gouty arthritis before treatment.(8)Similar diseases: individuals with CT or MRI imaging of neurological symptoms caused by non-vascular factors; individuals who have suffered from intracranial neurobiology or arteriovenous malformation, aneurysm or neuro-tumor, or individuals with cranial neuro-tumor visible in imaging; individuals with cerebral trauma, multiple sclerosis, cerebral parasites, seizures, hysterical paralysis, or cerebral amyloid angiopathy.(9)Individuals may be exposed to risks or damage by participating in this study from recruitment investigators’ points of view.(10)Disabled individuals (blind, deaf, dumb, mental disorders, mental disorders, and any other limb disability which can affect the evaluation of neurological impairment).(11)Individuals who have known or suspected of having a history of drug or alcohol abuse, or considered inappropriate by the recruitment investigators.(12)Allergic individuals: people who have known or suspected of being allergic to related substances in this study.(13)Individuals who are in other clinical trials or have participated in other drug trials in the past 3 months.

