### Collection and preservation of the baseline data

3.6

We have established the clinical research regulation, standardized operating procedure, data collection, and analysis of the multi-center randomized blind controlled trial. We will collect and evaluate 360 cases of patients with cerebral infarction or intercerebral hemorrhage no more than 3 months and the treatment will last 4 weeks.

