#### Visit 1 (Day-3∼0)

5.4.1

The basic demographic information, past medical and treatment history, course of the disease, complication, medication, and so on.General vital signs: temperature, respiration, heart rate, and blood pressure (measured after sitting still for 5 minutes).General physical examination and specialist examination.Laboratory examination: blood routine examination (red blood cell count, white blood cell count, platelet count, hemoglobin), urine routine examination, 4 coagulation tests (prothrombin time, activated partial thromboplastin time, plasma fibrinogen, and thrombin time), and 12-lead ECG examination.fMRI of the brain in the resting state and GAP-43 and MAP-2.Primary and secondary outcomes scale evaluation.Qualified patients (meeting all inclusion criteria and failing to meet all exclusion criteria) are randomly divided into groups based on the random number and they are informed of the treatment method.After the first treatment, the experimental group has an fMRI of the brain in the resting state.

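### The protocol places GAP-43 and MAP-2 at the border of an infarct, a site that haemorrhage patients lack and that no visit describes sampling

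*Protocol article*

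**What the plan says.** **Site.** Section 2.1 (Study design) ends its list of outcome measures with "2 brain function remodeling indexes, growth-associated protein-43 (GAP-43), and microtubule-associated protein-2 (MAP-2) in the infarction border zone".

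**Status and timing.** Section 5.1.2 lists both proteins among six secondary outcomes. The entry for Visit 1 (section 5.4.1) reads "fMRI of the brain in the resting state and GAP-43 and MAP-2", and the entry for Visit 4 on day 28 (section 5.4.3) is the same. None of these sections, nor the abstract, mentions a site.

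**Comparison.** For the modified Barthel index, WAB and water swallow test, section 5.2.2 names comparisons both among and within groups. For GAP-43 and MAP-2 it names only a comparison of values before and after treatment.

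**Population.** Section 3.6 plans for "360 cases of patients with cerebral infarction or intercerebral hemorrhage no more than 3 months". The inclusion criteria (section 3.3) first say "Meet the diagnostic criteria for cerebral infarction and intracerebral hemorrhage", but the onset rule that follows reads "The onset time of cerebral infarction or intracerebral hemorrhage is within 3 months". Section 3.4 excludes "individuals with progressive stroke or intracerebral hemorrhage after cerebral infarction or with disturbance of consciousness".

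**The concern.** A measurement site is part of an outcome's definition. The one given in section 2.1 is brain tissue next to an infarct. It does not fit a population in which some patients bled and had no infarct, and it does not fit a visit schedule that describes no sampling of such tissue.

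What is at stake is the conclusion. Section 2.1 presents the two proteins as indexes of brain remodelling. If levels in some other specimen were reported under that wording, the trial would appear to have observed remodelling at the lesion border when it had not. For haemorrhage patients the outcome as worded has no meaning, so it is unclear whether they are in or out of the comparison.

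A second issue bears on the same claim. A before-and-after change within an arm, in patients within three months of onset, mixes any treatment effect with natural recovery and routine rehabilitation. Only the contrast between randomised arms separates them.

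**Working it through.** The protocol gives no figure for these markers, so the check is mainly a comparison of sections.

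**1. Who is enrolled?** One inclusion line joins the two diagnoses with *and*; the onset rule and section 3.6 join them with *or*. Section 3.2.2 gives separate diagnostic criteria for each. The consistent reading is that either diagnosis qualifies.

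**2. Could haemorrhage patients still have the named site?** Section 3.4 removes haemorrhage that follows cerebral infarction. An eligible haemorrhage patient therefore does not enter with bleeding that followed an infarct, and the qualifying lesion has no infarct border.

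**3. Are the markers restricted to infarction patients?** No. Sections 5.1.2, 5.2.2, 5.4.1 and 5.4.3 apply them without regard to stroke type.

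**4. Is there a means of sampling the site?** Visits 1 and 4 list routine blood, urine and coagulation tests, an ECG, and then resting-state fMRI with GAP-43 and MAP-2 as an item of their own. No tissue sampling is described there or in the safety sections. The comparison needs two measurements per patient, about four weeks apart. That repeated sampling of the lesion border is not realistic in living rehabilitation patients is general reasoning, not a statement in the document; the schedule is consistent with it.

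**5. How many participants lack the site?** The haemorrhage share *s* is not stated. As an assumption, take *s* from 10% to 50%; the number without an infarct border is 360 × *s*.

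| Assumed haemorrhage share | Without the site | With an infarct |
|---|---|---|
| 10% | 36 | 324 |
| 20% | 72 | 288 |
| 30% | 108 | 252 |
| 40% | 144 | 216 |
| 50% | 180 | 180 |

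**6. Is the sample size touched?** No. Section 2.3 rests on effective rates of 80% and 90%, one-sided α of 0.05 and power of 0.80. With pooled variance and no continuity correction:

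n = [1.645 × √(2 × 0.85 × 0.15) + 0.842 × √(0.80 × 0.20 + 0.90 × 0.10)]² ÷ 0.10² ≈ 156.6, so 157 per group.

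Then 157 ÷ 0.90 = 174.4, so 175. Both match the protocol, and neither involves the markers.

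**The case against.** The strongest reply is that the phrase is a passing descriptor. It occurs once, at the end of a long overview list, and every section that sets status, timing or comparison leaves it out. It may be meant to say what the proteins reflect, not where they are sampled. Specimen and assay are details that an article may leave to the full protocol.

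Much of this stands. The silence on specimen and assay is not a finding. Because the markers are a separate scheduled item, their absence from the routine laboratory panel does not show that no specimen is planned. A reader might infer that the outcome cannot be obtained at all, or that no participant can supply it. The document does not support that, since the full protocol may name a workable specimen. Nor does it support assuming that the specimen is blood, or that the markers must be relabelled as exploratory.

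What does not stand is that nothing needs correcting. Section 2.1 introduces the list as what outcomes will be measured by, and the site it gives conflicts with the article's own eligibility rules. Even if the phrase only describes what the proteins are meant to reflect, it still does not fit haemorrhage patients.

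It can also be said that a between-arm analysis may be planned elsewhere. It may be, but the same item of section 5.2.2 names comparison among groups for the scales and not for the markers, so the text as written draws a distinction that should be removed.

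**Conclusion.** The point holds as a misstated measurement site for two of six secondary outcomes. For haemorrhage patients the mismatch follows from the protocol's own text. For infarction patients it rests on the absence of any described sampling and on general reasoning about feasibility. Its numerical size is unknown because the haemorrhage share is not stated; the range of 36 to 180 participants is illustrative only.

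The consequence is limited to what can be concluded from GAP-43 and MAP-2. The harm arises only if results are reported as findings at the lesion border, or if a within-arm change is read as a treatment effect. It merits correction but does not threaten the trial's main result.

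**What to change.** - **Section 2.1:** delete the closing words that place the markers at the infarct border.
- **Definition:** give one definition of GAP-43 and MAP-2, based on the specimen actually collected at Visits 1 and 4 and applied alike to infarction and haemorrhage. The sponsor must say what that specimen is.
- **Interpretation:** limit conclusions to levels in that specimen, and do not describe them as remodelling at the lesion border.
- **Section 5.2.2:** state that the change from Visit 1 to Visit 4 in each marker will be compared between the randomised arms, with the before-and-after change within each arm as supporting description.

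The cost is wording in sections 2.1 and 5.2.2 and one between-arm comparison per marker. It asks for no sampling beyond what is already planned and does not change the sample size or the primary outcomes. The downside is a more modest mechanistic claim.

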### Technology flow chart

2.2

The flow of the entire trial is shown in Figure 1.

**Figure 1 F1:**
[figure not shown]
The flow chart.

### Grouping

2.3

According to previous studies, the effective rate of the routine treatment group is 80 percent and the morbidity rate of eye-acupuncture and routine treatment group is 90 percent. Suppose *α* is 0.05 (one side) and *β* is 0.20. Calculated by PASS 11, the sample size in both groups is 157. With an estimated 10 percent dropout rate, the sample size is 175. Thus 360 patients will be recruited and divided into 2 groups in the study, with half of them (n = 180) in the control group (routine treatment group) and others (n = 180) in the experimental group (eye-acupuncture combined with routine treatment group).

**Table 1 T1:**

The specific case number in 6 centers.

### Randomization

2.5

Stratified block randomization will be used in the study based on the SAS proc plan sentence at the appropriate length. The seed is set as the running time of the program and the case number of the experimental group and the control group is in a ratio of 1:1. The serial number 001-360 which corresponds to a participant will be assigned to each center randomly. Centers are ordered in the alphabetical list by the initial letter of pinyin and offer treatment in increasing sequence.

### Concealment

2.6

Assignment sequence generated by random hiding is put into the sequentially encoded, sealed, and opaque envelope. Researchers will open the envelopes in sequence and assign participants into different groups.

### Cases of dropouts

2.7

1.When participants drop out of the study, researchers should try to contact them, ask for reasons, record the last time of medication, and finish the evaluation items.2.When participants drop out because of adverse events, researchers should take appropriate treatment and closely follow them up until the adverse events disappear or recover. Adverse events should be recorded and filled out in a case report form (CRF) and carried out statistical analysis.3.Researchers should record the main reasons for dropout.4.Whether participants drop out or not, all that have been recruited and have used the treatment number should be kept as records, which can be analyzed by intention-to-treat (ITT) analysis. There is no need to add cases after dropouts and all CRFs should be submitted to the statistical unit to make the analysis. The dropout rate of this clinical study should be under 10 percent.

### Data management

2.8

1.Clinical CRFs should be filled in accurately, completely, and timely by clinical researchers and the original records should be kept.2.To ensure the facticity and validity of the data, participants are asked to note the date and the total time they fill in the forms. The basic questionnaire survey should be completed within 14 days before the treatment starts and the information after enrollment should be completed within ±2 days of the stipulated date.3.To reduce dropouts and improve compliance, researchers and data collectors should remind the participants 1 day before the stipulated visit date.4.Data entry and modification: data entry and management are in the charge of data administrators from the statistical unit. Two data administrators input independently and proofread to make sure the accuracy of the data.5.Question management: data administrators make DRQ from the questions existed in the CRFs and send them to researchers. Researchers should answer and return DRQs as soon as possible. Then data administrators will modify, confirm and enter the data again according to the answer. The DRQs can be sent again if it is necessary.6.Data auditing and caging: clinical researchers, data administrators, and statistical analysts should audit the established database by the end of the study. After blind review and confirmation, the main researchers and statistical analysts will cage the data and the caging data file should not be modified.

### Statistical analysis

2.9

1.Full analysis set (FAS): FAS refers to the set of participants as close as possible to the intention-to-treat (ITT) analysis, including qualified cases and dropout cases.2.Per-protocol set (PPS): PPS, also known as effective cases or samples, is the set of participants who fully comply with the research protocol and complete stipulated information collection. PPS is a subset of FAS.3.Safety set (SS): SS refers to the set of participants who have received treatment at least one time. SS is used for security analysis.

## Objects/participants

3

Given that stroke in the convalescent stage is characterized by long course and relatively stable condition, a multi-center, randomized controlled trial has been designed to evaluate the clinical effect of eye-acupuncture combined with rehabilitation training therapy.

### Enrollment and recruitment of participants

3.1

1.Enrollment: subjects of the study will be recruited through television, radios, newspapers, communities, and hospitals on the principle of respecting subjects’ privacy and voluntary participation.2.Inclusion criteria: researchers in each subcenter are responsible to introduce the objectives, design, process, benefits, risks, and compensation in this study to subjects. According to the diagnostic criteria, inclusion criteria and exclusion criteria, researchers conduct preliminary screening for the recruited subjects. Those who meet the criteria are subjects who may participate in the study. They will sign the informed consent and their name, gender, age, address, telephone number, and other information should be recorded in detail.3.Screening: subjects who may participate in the study are further screened according to the diagnostic criteria, inclusion criteria, and exclusion criteria. Those who have met the criteria and signed the informed consent will conduct the basic questionnaire survey within 14 days before the treatment period. Subjects who can complete the questionnaire under guidance (more than 80% completion without logical problem) will be screened by physical and chemical examination indicators. The qualified ones will participate in clinical trials.

